Exercise	High-intensity interval training prescribed by physical therapist: – According to an adapted Wisloff protocol (33). – Borg scale to monitor intensity (34). – Training 3 times per week. Resistance exercises training: – With TheraBand OMNI-Resistance exercise bands. – Intensity will be based on participant's subjective perception, according to the perceived exertion scale (70%–80% 1 RM) – Frequency at least twice a week.	Moderate-intensity continuous exercise prescribed by physical therapist: – The intensity will be moderate, as tolerated – Borg scale to monitor intensity (34). – Frequency of training of 1 to 3 times per week, until completed 20 sessions in 10–12 weeks. Resistance exercices. – With available materials. – Moderate intensity – 1–2 times a week.
	Exercise volumes (interval plus resistance and continuous plus resistance) shall be equivalent between the experimental and control groups.	
Psychosocial support:	Based on social-cognitive theory (35) and delivered by a trained professional (occupational therapist or nurse), with self-efficacy as a focus, it will include: – Two face-to-face sessions in the first stage of the program: Education, self-monitoring and motivational interview. – One face-to-face session in the second stage of the program: promoting behavior changes by self-control and self-monitoring – Regular communication with patients will be supported by the use of mobile devices during the third and fourth stages of program. – Referral to a specialist will be considered if depression is detected in the screening.	Not applicable
Diet management	– Dietary plan supported by a nutritionist will be made together with the patient.	Not applicable

CR, cardiac rehabilitation; RM, repetition maximum; 6 MWT, 6 min walk test.

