### Experimental group

2.5

The participants randomly assigned to the experimental group will participate in a comprehensive, hybrid CR program, completed in 4 stages as presented in Table 3, and guided by the following 5 principles:
–Pragmatic: program implementation will be carried out as close to real-life as possible, that is to say, with the resources that a traditional program has in Chile, while adhering to minimum requirements and ensuring fidelity.–Interdisciplinarity: The design and implementation of the CR intervention will be carried out by an interdisciplinary team involving at least a physician, a nurse, a physiotherapist, a nutritionist, and a psychologist.–Progression: mainly of the intensity and frequency of exercise (36). All other interventions and the transition from the center-based to the home-based phase will have a pre-established progression.–Reproducibility: individualized exercise prescription, progression and transition to home-based CR will be explicit and reported.–Accompaniment: this is a key principle for monitoring progress and reinforcing interventions designed to promote adherence to interventions.

**Table 3 T3:** Comprehensive hybrid cardiac rehabilitation program protocol for the experimental group.

Stage	Characteristics	Duration
1. Fully supervised and center-based	– Supervised center-based sessions of high intensity interval training and resistance exercise. – Emphasis on education in the performance of the exercise, with the aim that it can be done independently in the future. – Intervention to promote adherence and diet management with two face-to-face sessions.	– Begins on admission to the program, and lasts for 4 weeks or earlier if the patient has learned to perform the strength exercises on their own, or later if the patient needs make-up some missed supervised sessions.
2. Transition to home-based	– Supervised center-based high intensity interval training with less frequency. – Reviewing the resistance exercises that are being done at home. – Intervention to promote adherence and heart-healthy diet will be monitored remotely in a weekly communication.	– Beginning at the end of stage 1 and continues through to 8 weeks.

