3. Home-based with monitoring	– Training is carried out at home and is monitored through a call at least once a week by the physiotherapist. – Psychosocial support and adherence to exercise, diet and medication will be promoted through phone calls once a week. – If necessary, a face-to-face session would be offered at this stage to reinforce any identified challenges and for progress evaluation.	– This stage will last 4 weeks or more, through to 12 weeks.
4. Home-based without monitoring	– The patient will do the training at home unsupervised. – Phone calls will be held once every two weeks for two months, and then once a month through to the 6 months. – These calls will be designed to reinforce adherence and resolve patient questions regarding exercise, diet, or medication.	– From week 12 to week 24.

The comprehensive, hybrid CR program will begin with an initial evaluation that includes all necessary assessments to prescribe exercise training as well as dietary and adherence promotion interventions (Table 3, Figure 3). The exercise component includes aerobic interval training and resistance exercises. The center-based training will be performed on an ergometer bike; as the CR program progresses, the training will be adapted to a modality that can be undertaken by the patient at home, such as using of a footstool, static bike if it is available, or walking outdoors.

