**Figure 3 F3:**
[figure not shown]
Schematic overview of the four stages of the experimental intervention.

For the aerobic interval training, the Wisløff protocol (33), with long work intervals, will be adapted. Each session will consist of a 10 min warm-up, followed by 20 min of high-intensity interval training, with sets from 1 min progressing to 4 min bouts at 90%–100% VO_2_ max or over level 18 in the Borg scale, with a safety range based on the heart reserve rate (HRR) between 60% and 90% (37). This will be interjected with active pauses at an intensity below ventilatory threshold 1 or level 12–13 on the Borg scale (safety range set at 40%–60% HRR) (38) with a duration from 3 to 5 min. When the patient is training with another device or modality, the speed or power of the exercise will be modified to achieve the intensity targets. The Borg scale (34), rather than heart rate, will be used to monitor intensity, as it is easier for the patient, who will be expected to monitor the exercise intensity on their own once they transition to home-based. Nevertheless, at the beginning of the program, the therapist will monitor patient's heart rate in parallel to ensure the equivalence with the Borg scale. The session will end with a 10 min cool-down period. The frequency of training will be 3 times per week (38).

Resistance exercises training will be performed with an elastic resistance band and a weighted bag. The recommendation will be to perform the exercises at least twice a week, and will consist of six exercises involving the major muscle groups. The load and intensity of the exercises will progress throughout the program from light to heavy elastic resistance. The intensity for each phase will be established according to the patient's rating based on the perceived exertion scale with Thera Band OMNI-Resistance exercise bands. The target is to achieve 8 to 12 repetitions of each exercise. Exercises will be performed at a cadence of 1 s for the concentric phase and 1 s for the eccentric phase. Sets for upper body exercise progress from 3 to 5 and for lower body exercise from 2 to 4. A rest period of 2 min will be allowed between sets (39).

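### Table 2 says exercise volume shall be equivalent in the two arms, but the printed schedules, read plainly, prescribe 36 aerobic sessions against 20 by week 12, and home training to week 24 in one arm only

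*Protocol article*

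**What the plan says.** The equivalence statement closes the exercise row of Table 2 (section 2.4) and spans both columns: "Exercise volumes (interval plus resistance and continuous plus resistance) shall be equivalent between the experimental and control groups". No unit of volume, tolerance or period is given.

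**Experimental arm.** Table 2 gives three interval sessions a week. Section 2.5 repeats this without tying it to a stage: "The frequency of training will be 3 times per week". A session has "a 10 min warm-up, followed by 20 min of high-intensity interval training", then a cool-down. The work bouts have a safety range of 60%–90% of heart rate reserve (HRR) and the active pauses 40%–60%. Table 3 sets out four stages:

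- Stage 1 lasts four weeks, but may end sooner or later.
- Stage 2 runs to week 8: "Supervised center-based high intensity interval training with less frequency".
- Stage 3 runs to week 12: "Training is carried out at home and is monitored through a call at least once a week by the physiotherapist".
- Stage 4: "The patient will do the training at home unsupervised", timed as "From week 12 to week 24".

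Resistance work is at least twice a week at 70%–80% of 1 RM.

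**Control arm.** Table 2 and section 2.6 give 20 supervised sessions over 10–12 weeks. Continuous exercise rises from 10 to 30 minutes, as tolerated, at 40%–60% HRR. Resistance work is once or twice a week at 50%–60% of 1 RM. No home training is described.

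**The concern.** The sentence tells the reader that exercise volume is held constant between arms, so that a fitness difference could not come from one arm being given more exercise. The frequencies printed in the same table point the other way.

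This matters for interpretation. VO2max drives the sample size and is the basis of the hypothesis, and the Introduction itself links a larger rehabilitation dose to better outcomes. If volume is believed to be matched, a VO2max gain will be credited to interval training, hybrid delivery or psychosocial support at equal dose. Therapists are also left with two instructions, a fixed frequency and a matched volume, that are hard to follow together.

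**Working it through.** The plan gives no volume figure to reproduce. Its statement implies an experimental-to-control ratio of 1. The check is sessions = weeks × weekly frequency, and aerobic minutes = sessions × length of the main block, leaving out warm-up and cool-down. The 20-minute block is taken to include the pauses.

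**1. Aerobic sessions to week 12, plain reading.** At three a week in each of stages 1 to 3: 3×4 + 3×4 + 3×4 = 36. Controls: 20. Session ratio 36/20 = 1.8. If the frequency stays at three a week, moving the boundary between stages changes nothing.

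**2. Aerobic sessions, reduced readings.** These take the lower frequency in stage 2 to mean less training in total, not only fewer supervised visits.

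- Stage 2 at two a week: 12 + 8 + 12 = 32.
- Stage 2 at one a week: 12 + 4 + 12 = 28.
- Stage 1 ending at two weeks (an assumption; no minimum is stated), then stage 2 for six weeks at one a week: 6 + 6 + 12 = 24.

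So 28 is not a floor.

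**3. Control minutes.** The shape of the progression is not given, so three are assumed.

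- Linear from 10 to 30 minutes: 20 × 20 = 400.
- 30 minutes reached by session 10: 10×20 + 10×30 = 500.
- 30 minutes reached by session 5: (10+15+20+25+30) + 15×30 = 550.

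The ceiling of 20×30 = 600 cannot be reached, because sessions start at 10 minutes.

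**4. Ratio of aerobic minutes, experimental to control.**

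| Experimental sessions | Minutes | vs 400 | vs 500 | vs 550 |
|---|---|---|---|---|
| 36 | 720 | 1.80 | 1.44 | 1.31 |
| 28 | 560 | 1.40 | 1.12 | 1.02 |
| 24 | 480 | 1.20 | 0.96 | 0.87 |

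On the plain reading, even the unreachable ceiling leaves a gap: 720/600 = 1.20. On the reduced readings the range includes 1.

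**5. Intensity.** The pauses share the control arm's 40%–60% HRR range and the bouts lie above it. Intensity therefore does not offset a larger number of minutes.

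**6. Resistance sessions to week 12.** Experimental: at least 2×12 = 24. Control: from 1×10 = 10 to 2×12 = 24. The counts meet only if controls do two a week for 12 weeks and the experimental arm does its minimum. The prescribed load still differs (70%–80% against 50%–60% of 1 RM).

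**7. Supervised sessions only.** Stage 1 gives 3×4 = 12. Stage 2 at two a week gives 8. The total is 20 against 20.

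**8. After week 12.** The experimental arm has a further 12 weeks of home training and the control arm has no prescribed programme. Table 3 does not restate a frequency for stage 4, so no ratio to week 24 is calculated.

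**The case against.** The strongest reply is that the sentence concerns volume, aerobic plus resistance, while the clear discrepancy is in session counts. Control resistance sets and minutes are not given, so total volume cannot be computed. This stands. A reader might take 1.8 as a volume ratio, or take 28 sessions as a floor that rules out equality. Neither is supported, because 24 sessions is possible on a permitted reading and aerobic minutes can then fall below the control total.

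A second reply is that supervised sessions were meant. They match at 20 each if stage 2 is twice weekly, which is the attendance that Table 1 requires in month 2, and a linear control progression also averages 20 minutes. This is a plausible intention, but the sentence does not say it, and section 2.7 counts home activities as prescribed exercise for adherence.

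Third, this is a condensed article, and the full protocol may hold a matching rule. Such a rule would have to override the frequencies printed here.

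Fourth, the Discussion already concedes that the effects of components cannot be separated, and the stated hypothesis compares packages. Both are true, but a general caveat does not withdraw a specific statement that volume is equal. A reader might also infer that unequal volume biases the trial. It does not: the randomised comparison of the two programmes as delivered remains valid.

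**Conclusion.** The point holds as an inconsistency between the equivalence statement and the schedules on their plain reading. To week 12 the experimental arm is prescribed 36 aerobic sessions against 20, with harder bouts and with resistance sessions at least as frequent and at a higher load. It then has home training to week 24 that controls do not.

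The size is firm only as a session ratio of 1.8, and only if three sessions a week applies throughout stages 1 to 3. In aerobic minutes the plain reading gives 1.31 to 1.80 under the assumed control progressions. The lowest reading shown gives 0.87 to 1.20. Total volume is unknown.

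The consequence is one of interpretation. A VO2max difference at 3 or 12 months cannot be presented as an effect at equal exercise volume. The sample size, which rests on an assumed difference and standard deviation, is not touched.

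**What to change.** - Delete the equivalence sentence from Table 2 or, if supervised sessions were meant, limit it to those and state the stage 2 frequency that makes them match.
- State that the experimental arm is prescribed more aerobic sessions to week 12 and home training to week 24. If stage 2 is meant to reduce total training, say so and give the number.
- Report prescribed and completed sessions by arm, and minutes where recorded, beside the VO2max result. Show staff-recorded attendance separately from diary-reported home sessions, since the two differ in reliability.
- Do not interpret a VO2max difference as an effect at equal exercise volume.

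The cost is a small change of protocol wording and one descriptive table from attendance and diary records that section 2.7 and Table 4 already plan. Neither programme changes and no new data are collected.

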### Experimental group

2.5

The participants randomly assigned to the experimental group will participate in a comprehensive, hybrid CR program, completed in 4 stages as presented in Table 3, and guided by the following 5 principles:
–Pragmatic: program implementation will be carried out as close to real-life as possible, that is to say, with the resources that a traditional program has in Chile, while adhering to minimum requirements and ensuring fidelity.–Interdisciplinarity: The design and implementation of the CR intervention will be carried out by an interdisciplinary team involving at least a physician, a nurse, a physiotherapist, a nutritionist, and a psychologist.–Progression: mainly of the intensity and frequency of exercise (36). All other interventions and the transition from the center-based to the home-based phase will have a pre-established progression.–Reproducibility: individualized exercise prescription, progression and transition to home-based CR will be explicit and reported.–Accompaniment: this is a key principle for monitoring progress and reinforcing interventions designed to promote adherence to interventions.

**Table 3 T3:** Comprehensive hybrid cardiac rehabilitation program protocol for the experimental group.

Stage	Characteristics	Duration
1. Fully supervised and center-based	– Supervised center-based sessions of high intensity interval training and resistance exercise. – Emphasis on education in the performance of the exercise, with the aim that it can be done independently in the future. – Intervention to promote adherence and diet management with two face-to-face sessions.	– Begins on admission to the program, and lasts for 4 weeks or earlier if the patient has learned to perform the strength exercises on their own, or later if the patient needs make-up some missed supervised sessions.
2. Transition to home-based	– Supervised center-based high intensity interval training with less frequency. – Reviewing the resistance exercises that are being done at home. – Intervention to promote adherence and heart-healthy diet will be monitored remotely in a weekly communication.	– Beginning at the end of stage 1 and continues through to 8 weeks.
3. Home-based with monitoring	– Training is carried out at home and is monitored through a call at least once a week by the physiotherapist. – Psychosocial support and adherence to exercise, diet and medication will be promoted through phone calls once a week. – If necessary, a face-to-face session would be offered at this stage to reinforce any identified challenges and for progress evaluation.	– This stage will last 4 weeks or more, through to 12 weeks.
4. Home-based without monitoring	– The patient will do the training at home unsupervised. – Phone calls will be held once every two weeks for two months, and then once a month through to the 6 months. – These calls will be designed to reinforce adherence and resolve patient questions regarding exercise, diet, or medication.	– From week 12 to week 24.

The comprehensive, hybrid CR program will begin with an initial evaluation that includes all necessary assessments to prescribe exercise training as well as dietary and adherence promotion interventions (Table 3, Figure 3). The exercise component includes aerobic interval training and resistance exercises. The center-based training will be performed on an ergometer bike; as the CR program progresses, the training will be adapted to a modality that can be undertaken by the patient at home, such as using of a footstool, static bike if it is available, or walking outdoors.

**Figure 3 F3:**
[figure not shown]
Schematic overview of the four stages of the experimental intervention.

For the aerobic interval training, the Wisløff protocol (33), with long work intervals, will be adapted. Each session will consist of a 10 min warm-up, followed by 20 min of high-intensity interval training, with sets from 1 min progressing to 4 min bouts at 90%–100% VO_2_ max or over level 18 in the Borg scale, with a safety range based on the heart reserve rate (HRR) between 60% and 90% (37). This will be interjected with active pauses at an intensity below ventilatory threshold 1 or level 12–13 on the Borg scale (safety range set at 40%–60% HRR) (38) with a duration from 3 to 5 min. When the patient is training with another device or modality, the speed or power of the exercise will be modified to achieve the intensity targets. The Borg scale (34), rather than heart rate, will be used to monitor intensity, as it is easier for the patient, who will be expected to monitor the exercise intensity on their own once they transition to home-based. Nevertheless, at the beginning of the program, the therapist will monitor patient's heart rate in parallel to ensure the equivalence with the Borg scale. The session will end with a 10 min cool-down period. The frequency of training will be 3 times per week (38).

Resistance exercises training will be performed with an elastic resistance band and a weighted bag. The recommendation will be to perform the exercises at least twice a week, and will consist of six exercises involving the major muscle groups. The load and intensity of the exercises will progress throughout the program from light to heavy elastic resistance. The intensity for each phase will be established according to the patient's rating based on the perceived exertion scale with Thera Band OMNI-Resistance exercise bands. The target is to achieve 8 to 12 repetitions of each exercise. Exercises will be performed at a cadence of 1 s for the concentric phase and 1 s for the eccentric phase. Sets for upper body exercise progress from 3 to 5 and for lower body exercise from 2 to 4. A rest period of 2 min will be allowed between sets (39).

During supervised exercise sessions, patients will be educated on how to perform exercise at home and monitor intensity, using the Borg rating of perceived exertion (RPE) or heart rate (HR). Progression will be individualized according to the progress in perceived exertion, to maintain the intensity during the whole program (36).

Over three sessions, with the first being face-to-face and subsequently via phone calls, diet management will be promoted with a nutritionist. This will include an initial evaluation, with a dietary plan agreed to prevent malnutrition and eat heart-healthily, avoid excessive salt intake (>5 g/day), improve energy and protein intake according to their exercise prescription, and achieve or maintain healthy body weight (40).

Psychosocial support and education to promote adherence to CR will be provided based on Social-cognitive theory, in which self-efficacy is a central concept (35). After an initial assessment of self-efficacy, the intervention will start with two face-to-face sessions in the first stage of the program: the first one with education about the patient's diagnosis and treatments to improve health and QoL indicators, and the second one to conduct a motivational interview (41, 42) and teach the self-monitoring behavioral change technique (43, 44). An additional third face-to-face session in the second stage will promote behavioral change through the techniques of self-control and contingency management through self-monitoring by the patient. Subsequent to these sessions and to further support the behavioral change necessary to achieve adherence to treatment, continuous communication with patients will occur with the use of mobile devices, by phone calls made by a trained collaborator. Specifically, weekly calls will be held in the third stage of the program, and every two weeks in the fourth stage (45, 46). If, during these conversations, the patient expresses the need for any supervised exercise sessions, they will be scheduled with the physiotherapist. Finally, referral to a specialist will be considered if depression is suspected upon screening.

### Control group

2.6

The patients in the control group will receive the conventional center- and exercise-based CR at the participating centers. These programs consist of an initial assessment as well as medical and nurse management. The exercise component will comprise continuous aerobic exercise sessions plus resistance exercises. Continuous moderate exercise sessions will be of 10 min duration at the beginning of the program, and progress to 30 min by the end, as tolerated by each patient; the patient may rest between the exercises to complete the maximum tolerable exercise time. The resistance exercise training will include polyarticular and monoarticular movements against mechanical resistance or free weight. The intensity of this training will be moderate as per the Borg perceived exertion scale (34), specifically as “fairly light to somewhat hard” (score 12–13) or 50%–60% of the estimation of 1 RM. Additionally, a safety range will be set at 40%–60% HRR, which corresponds to moderate intensity. These programs typically last 10–12 weeks (3 months) with 20 supervised exercise sessions.

